Regardless of the wearable sensors used or the freezing protocol, the accuracy of detection is sensitive to the type of algorithm [9,11,12,23]. Yet, the algorithms used to detect FoG episodes are controversial, especially for real-time detection. The threshold method provides a straightforward approach to the implementation and interpretation of algorithms. In this context, the freezing index—defined as the ratio between the power bands of freezing (3-8 Hz) and locomotion (0.5-3 Hz)—is the most commonly used feature in threshold-based algorithms [9,11,12,23]. This single feature accurately detects many FoG episodes (sensitivity: 84.3%; specificity: 78.4% [24]), but detection fails when no motion is observed and voluntary stops may be mistakenly classified as FoG [17]. Adding multiple indices can enhance algorithm performance, but it also increases complexity and the difficulty of tuning thresholds [25,26]. To address these limitations, machine learning (ML) algorithms have been developed to improve FoG detection performance. Indeed, ML algorithms could better fit the model to increase the accuracy of the models; this is a subfield of artificial intelligence that gives an algorithm the ability to learn without being explicitly programmed [12]. Among the various ML algorithms, support vector machine, multilayer perceptron, and ensemble classifiers (eg, random forest or AdaBoost) have proven to be the most efficient. Determining the best ML algorithm is challenging due to the highly heterogeneous nature of the training data. A limitation of ML algorithms is that training the model and processing the data can require high computational cost. Fortunately, advances in computer technology now offer the possibility of early or real-time detection with ML models [12].

The primary objective is to assess the accuracy of the optimal combination of wearable sensors for detecting FoG episodes in patients with PD. The secondary objectives of this study include measuring the specificity, sensitivity, positive predictive value (PPV), and negative predictive value (NPV) of the optimal combination of wearable sensors for detecting FoG episodes. Regarding the setup, we also aim to compare its performance (accuracy, sensitivity, specificity, PPV, and NPV) across various clinical and medical conditions.

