## Methods

### Study Design and Participants

This study is a single-center, prospective cohort trial (DetectFoG) involving patients with PD with FoG at the University Hospital of Rennes. Patients will be recruited from the neurology department of University Hospital of Rennes during their visit to the neurologist. This study aims to include a total of 18 patients. To mitigate potential issues such as withdrawal of consent, absence of FoG during neurologist annotation, loss of follow-up (failure to attend the second visit), or inability to complete the required number of passages (fewer than 6), initially, 20 patients will be enrolled. Participants experiencing any of these issues will be excluded from the study.

Inclusion criteria will include patients older than 18 years diagnosed with PD according to the UK Brain Bank criteria. Patients must self-report as freezers, scoring between 1 and 3 on question 13 of the Movement Disorder Society-Unified Parkinson’s Disease Rating Scale (MDS-UPDRS) II [27], and be capable of walking 30 m without assistance to complete the freezing-provoking path. Exclusion criteria will apply to patients scoring less than 20 out of 30 on the Montreal Cognitive Assessment [28] who are unable to give informed consent and those with neurological, orthopedic, or rheumatic comorbidities that could impact gait and ability.

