### Data Analysis

#### Features Extractions

Each window of data will undergo normalization to achieve zero mean and unit variance. Our study distinguishes itself through an exhaustive exploration of features aimed at identifying FoG episodes. From each window, signal features will be extracted from both the time and frequency domains. A comprehensive array of features will be included, such as the number, duration, and length of acceleration or angular velocity reversals, kurtosis, and skewness [14]. Furthermore, we will incorporate metrics such as the magnitude of mean and SD of signals, as well as specific metrics related to smoothness such as spectral arc length measure [39] and the freezing ratio [40]. Nonlinear modeling features, such as sample entropy or Lyapunov exponent, which quantify gait regularity and complexity, will also be used [41]. Furthermore, measures of inter- and intralimb coordination will be integrated to highlight specific limb dynamics during FoG episodes. Feature selection will be conducted using Relief-F, chosen for its suitability in our application over methods such as minimum redundancy maximum relevance ranking [20]. This approach ensures that the selected features are highly relevant to distinguishing FoG episodes, thereby optimizing the accuracy and effectiveness of our analysis.

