#### Model Training

The top-ranked features identified through Relief-F will be used in a decision tree (DT) model for classifying windows of data. The DT model will be tested using 5 and 10 decision splits and with various sets of top-ranked features ranging from 5 to 20. The performance of the DT model will be evaluated using metrics such as accuracy, sensitivity, specificity, PPV, and NPV. The model’s performance will be determined based on the classification of each window as true positive (TP), true negative (TN), false positive (FP), or false negative (FN), comparing the model’s classifications with the experts’ identification of FoG episodes on video recordings (Figure 4).

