#### Model Validation

The model validation will use the leave-one-subject-out (LOSO) cross-validation technique to assess its performance across participants and accommodate the considerable variability between participants. While some studies [20,42] advocate for the leave-one-freezer-out (LOFO) cross-validation technique to avoid overrepresentation of patients without FoG in training and validation sets, our study focuses on participants who have experienced at least 1 episode of FoG during their initial visit. Consequently, each patient will have FoG episodes, making the LOSO approach more suitable for our validation process.

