#### Primary Outcome

The main objective of our study is to identify the most relevant features and locations of wearable sensors for detecting FoG episodes. The Relief-F technique will rank features extracted from data collected by all sensor segments. The top-ranked features across all subjects will indicate the most critical sensors for detecting FoG episodes, and these features will be used in model training and validation. The LOSO method will be used for validation, and accuracy will be computed for each subject. Furthermore, Relief-F analysis will be conducted individually for each subject to potentially reveal redundancy in the top-ranked features across subjects. Feature extraction, selection, model training, and validation will be implemented using Python 3.0 (PythonLabs) scripts.

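### Features are ranked on all subjects' FoG labels before leave-one-subject-out validation, so the primary accuracy tends to be too high for a new patient

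*Protocol article*

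**What the plan says.** All references are to the protocol article.

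- Introduction, on the aim: "The primary objective is to assess the accuracy of the optimal combination of wearable sensors for detecting FoG episodes in patients with PD".
- Study Design and Participants: "This study aims to include a total of 18 patients", with 20 enrolled to allow for exclusions.
- Features Extractions: "Feature selection will be conducted using Relief-F". The stated purpose is that "This approach ensures that the selected features are highly relevant to distinguishing FoG episodes".
- Primary Outcome: Relief-F ranks the features from all sensors. "The top-ranked features across all subjects will indicate the most critical sensors for detecting FoG episodes, and these features will be used"; the same sentence goes on to name the stage: "these features will be used in model training and validation". LOSO, with accuracy per subject, comes in the next sentence. A second Relief-F analysis is run subject by subject, to look for redundancy.
- Model Training: "The DT model will be tested using 5 and 10 decision splits and with various sets of top-ranked features ranging from 5 to 20".
- Model Validation: "The model validation will use the leave-one-subject-out (LOSO) cross-validation technique to assess its performance across participants".

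The article describes no ranking repeated inside the folds, no separate test set and no external data.

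**The concern.** LOSO answers one question: how well would the detector work in a patient it has never seen? That holds only if everything learned from labelled data, including which features to keep, is learned without the left-out patient. Relief-F is supervised. It scores a feature by how well it separates neighbouring windows with different labels, and here the labels are the experts' FoG annotations. If the ranking pools all subjects, the left-out patient's labels have already shaped the model before that patient is tested.

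What is at stake is the number the study sets out to report. With few patients and a large pool of candidate features from seven sensors, some features will rank highly partly because they happen to suit these particular patients. Testing on the same patients then rewards that coincidence. Sensitivity and the other performance measures come from the same window classifications.

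**Working it through.** The article gives no expected accuracy and no derivation of 18, so there is no planned figure to reproduce. The check has two parts: the order of the steps, and illustrative simulation of the direction and size.

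**1. Order of the steps.** Selection uses FoG labels (Features Extractions). It is done across all subjects, and the resulting features serve both training and validation (Primary Outcome). LOSO follows. Ranking inside the folds would produce up to 18 feature sets, which does not fit a single set used for both purposes. The subject-by-subject Relief-F run is not a training-fold ranking either. With 18 subjects, each held-out patient is 1/18 = 5.6% of the subjects behind the ranking used to test that patient.

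**2. First simulation.** It compares ranking on all 18 subjects with re-ranking on the 17 training subjects of each fold. Assumptions not in the article: 300 features, 60 non-overlapping windows per subject, top 10 features, 10 splits, between-subject SD of 0.7 in feature effects, a common FoG shift of 0 or 0.7 SD in 10 features, and FoG in 50% or 20% of windows. There were 24 runs per scenario.

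| FoG share, common shift | Accuracy, all-subject ranking | Accuracy, in-fold ranking | Difference (SE), points | Sensitivity difference | Specificity difference |
|---|---|---|---|---|---|
| 50%, none | 60.6% | 56.0% | +4.6 (0.8) | +8.3 | +0.9 |
| 20%, none | 78.3% | 77.7% | +0.7 (0.2) | +3.9 | -0.1 |
| 50%, 0.7 SD | 71.5% | 68.0% | +3.5 (0.6) | +6.7 | +0.3 |
| 20%, 0.7 SD | 81.7% | 80.2% | +1.5 (0.2) | +8.2 | -0.1 |

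Differences were rounded after subtraction.

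The columns agree with each other through: accuracy difference = share × sensitivity difference + (1 − share) × specificity difference.

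- 50%, no shift: 0.5 × 8.3 + 0.5 × 0.9 = 4.6.
- 20%, no shift: 0.2 × 3.9 + 0.8 × (−0.1) = 0.7.

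This shows why a FoG minority hides the effect in accuracy: the gain is in sensitivity, which then carries little weight.

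**3. Second simulation.** No feature has a population-level FoG effect, so true accuracy is 50%. It used 18 subjects, 630 candidate features (assumed), trees with 5 or 10 splits, and 17 replicates; no standard errors are available.

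- Without between-subject baseline offsets: 59.2% (all subjects) against 50.9% (in fold), a difference of +8.3 points.
- With large offsets: 48.0% against 48.7%, a difference of −0.7 points, in effect none.

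**4. Choice of tree settings.** This matters only if the setting is picked by its LOSO accuracy. In the second simulation with in-fold ranking, the best of 10 settings exceeded the average by 55.5 − 50.9 = 4.6 points, and with offsets by 53.4 − 48.7 = 4.7 points. In the first simulation with in-fold ranking, the best of 6 settings exceeded the fixed setting by 1.1 to 2.1 points (for example 58.1 − 56.0 = 2.1), and part of that may be a genuinely better setting.

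**The case against.** **A condensed article may simply omit nesting.** Silence would indeed be no finding. Here, however, the text states the pooled ranking and its use in both stages. A fuller document that ranks inside the folds would contradict this section, which would still need correcting. The article does not literally say that Relief-F is run only once; that is the plain reading of one set of features serving both stages.

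**An all-subject ranking suits the sensor-location aim.** This stands. The Primary Outcome section frames the main objective as finding relevant features and locations, and a pooled ranking is a fair description for that. The Introduction, however, makes accuracy the primary objective, and that figure is what the leak affects.

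Four stronger readings are tempting but not supported:

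- *The reported accuracy is the maximum over 32 tuned trees.* Model Training says the settings will be tested, not that the best one's LOSO accuracy will be reported. The optimum in the Introduction concerns the sensor combination. The count of 32 (2 × 16) needs every integer from 5 to 20; steps of five would give 2 × 4 = 8.
- *The optimism may reach 15 points.* That compares 65% (all-subject ranking and best of 10 settings together) with a true 50%. It mixes the ranking leak with an unstated choice of setting and assumes balanced classes.
- *Feature scaling leaks as well.* Features Extractions normalises each window on its own, so no scaling across subjects is described.
- *Every performance measure is inflated alike.* Specificity hardly changed in the simulation, and PPV and NPV were not computed.

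**Conclusion.** The point holds and should be settled before the analysis. As written, the plan lets each held-out patient help choose the features on which that patient is tested, so LOSO accuracy tends to overstate performance in a new patient. This follows from a stated rule, not from a missing detail.

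The size is uncertain. Across the two simulations the ranking leak ran from −0.7 to +8.3 points of accuracy, so roughly 0 to 8. It was 0.7 to 1.5 points with FoG in 20% of windows, where sensitivity still rose by 3.9 to 8.2 points. The article gives no expected FoG share. Its rule that a window counts as FoG only if all 2 seconds are FoG pushes towards a minority, which makes the lower end more plausible for accuracy and makes sensitivity the measure to watch. The result also depends on the number of features and the variation between patients, neither of which the article quantifies.

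Optimism from choosing tree settings is conditional: it arises only if that choice uses LOSO accuracy in the same patients.

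**What to change.** Replace the sentences on ranking and validation in the Primary Outcome section with text such as:

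> Within each LOSO fold, Relief-F ranking, and any choice of sensors, number of features and number of splits, use the training subjects only (inner LOSO for tuning). The resulting model is applied once to the held-out subject, and accuracy is summarised over held-out subjects.

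Keep the all-subject Relief-F ranking as a descriptive result on feature and sensor location, not as input to the validated model.

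The change needs no new data and no extra burden for patients. According to the article's Results section, 3 patients had been recruited by August 2024 and analysis was to wait until all data were in. The costs are:

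- **Computing.** Relief-F is repeated in each of 18 folds and, with inner LOSO, on a further 18 × 17 = 306 training sets of overlapping windows. This is feasible but more than one ranking.
- **Reporting.** Selected features may differ between folds, so the report should say how often each feature and sensor was chosen.
- **Result.** The reported accuracy will probably be slightly lower.

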#### FoG Measurement

##### IMU Measurements

Patients will wear the Trigno Avanci IMU (Delsys; Figure 3), which includes a triaxial accelerometer, gyroscope, and magnetometer. Data will be transmitted via Bluetooth and collected using the Delsys application programing interface and then transferred to QTM 2020 software (Qualisys). The software manages recording at a sampling frequency of 148.15 Hz and synchronizes with cameras. While this sampling frequency is higher than that in some studies, it has been previously used, similar to the approach taken by Camps et al [37]. This frequency is selected to ensure that all nuances associated with FoG, particularly micromovements, are captured. IMU data will also undergo windowing with a 2-second window length and a 0.4-second shift. A trained operator will position the sensors manually, aligning them with anatomical axes. Seven IMUs will be placed as follows: 1 on each thigh (lateral side, upper third), 1 on each fibula (upper third), 1 on each foot (below the lateral malleolus), and 1 at lumbar level (L5).

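### The primary analysis picks sensors from one Relief-F feature ranking and never compares sensor sets, so it gives no evidence that the chosen sensors are the optimal combination

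*Protocol article*

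**What the plan says.** All references are to the protocol article.

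- **Objective, Introduction:** "The primary objective is to assess the accuracy of the optimal combination of wearable sensors for detecting FoG episodes in patients with PD". The Abstract (Methods), the Discussion and the Conclusions repeat the aim of finding or assessing the most effective combination. The Discussion adds that placements need examining both singly and together.
- **Objective, Primary Outcome section:** "The main objective of our study is to identify the most relevant features and locations of wearable sensors for detecting FoG episodes".
- **Sensors, IMU Measurements:** "Seven IMUs will be placed as follows". They go on both thighs, both fibulas and both feet, with one at L5.
- **Selection method, Features Extractions:** "Feature selection will be conducted using Relief-F, chosen for its suitability in our application over methods such as minimum redundancy maximum relevance ranking".
- **Ranking, Primary Outcome section:** "The Relief-F technique will rank features extracted from data collected by all sensor segments".
- **Step from ranking to sensors, same section:** "The top-ranked features across all subjects will indicate the most critical sensors for detecting FoG episodes". The same features then go into model training and leave-one-subject-out (LOSO) validation, with accuracy computed for each subject. Relief-F is also run separately in each subject, to look for redundancy of the leading features across subjects.
- **Alternatives tested, Model Training:** "The DT model will be tested using 5 and 10 decision splits and with various sets of top-ranked features ranging from 5 to 20".

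**The concern.** The question is about sets of sensors; the analysis is about a list of features. Whether a set is optimal can be judged only against other sets, and no described step fits or scores models on different sensor sets.

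The ranking is a weak substitute because Relief-F gives every feature its own relevance weight and takes nothing off for repeating another feature. The article prefers it to minimum redundancy maximum relevance, which does penalise repetition. Overlap is plausible here: three of the four locations are left–right pairs, the signals are triaxial, and many time- and frequency-domain features come from each sensor. The leading 5 to 20 features could therefore repeat one signal, while a sensor that adds different information falls below the cut. The per-subject ranking shows whether the same features recur in different people; it does not show whether two sensors carry the same information.

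At stake is the study's main deliverable: how many sensors to wear, and where.

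**Working it through.** The article gives no derived figure to reproduce on this point. The check counts what could be compared, counts what is compared, and then illustrates how the ranking can behave.

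**1. Possible sensor sets** (IMU Measurements: 7 units, 4 locations)
- Non-empty sets of locations, bilateral sensors kept as pairs: 2^4 − 1 = 15.
- Non-empty sets of individual sensors: 2^7 − 1 = 127.

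**2. What is compared** (Model Training)
- 2 split settings × 16 feature counts, if every integer from 5 to 20 is used: 2 × 16 = 32. The article gives no step size; steps of 5 would give 2 × 4 = 8.
- All these settings are nested cuts of one pooled ranking. Changing the cut may incidentally change which sensors contribute, but no setting is defined by sensor.
- Sensor sets compared with one another by design: 0 of 15, or 0 of 127.

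**3. Illustration of the ranking** (every input is an assumption)

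Sensors A and A′ see the same latent signal, and sensor B sees an independent one. Each yields 10 features (latent signal plus noise, SD 0.2). There are 300 training windows, 10 neighbours and 20 replicates, and a linear discriminant stands in for the decision tree. The best two-sensor set is A + B by construction. Class separations are in SD units. Loss is the accuracy of A + B with the same number of features, minus the accuracy of the Relief-F list.

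| Separation A, B | Features | A and A′ both listed | B absent | Accuracy, Relief-F list | Accuracy, A + B | Loss |
|---|---|---|---|---|---|---|
| 2, 0.7 | 5 | 100% | 95% | 0.839 | 0.851 | 0.012 |
| 2, 0.7 | 10 | 100% | 80% | 0.838 | 0.847 | 0.009 |
| 2, 0.7 | 20 | 100% | 70% | 0.833 | 0.843 | 0.010 |
| 2, 1 | 5 | 65% | 60% | 0.805 | 0.863 | 0.058 |
| 2, 1 | 20 | 100% | 45% | 0.841 | 0.853 | 0.012 |
| 1.5, 1 | 5 | 15% | 0% | 0.723 | 0.810 | 0.087 |
| 1.5, 1 | 20 | 100% | 0% | 0.798 | 0.800 | 0.002 |
| 1.5, 1.5 | 5 | 0% | 0% | 0.767 | 0.849 | 0.082 |
| 1.5, 1.5 | 20 | 100% | 0% | 0.842 | 0.840 | −0.002 |

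Three patterns appear:
- The list keeps both duplicates and usually drops the complementary sensor (2, 0.7).
- A short list fills with one sensor's features (1.5, 1.5 with 5 features: all five come from B).
- Accuracy is hardly affected but the redundant sensor stays listed (1.5, 1 with 20 features), which is still the wrong answer on how many sensors to wear.

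A repeat with a tree of 5 or 10 splits and noisier features (SD 0.5) lost less than 1 percentage point at 20 features in every setting tried. Losses of several points arose only with short lists and a separation of 1.5 for A.

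**The case against.** - **Relief-F is not a one-feature-at-a-time filter.** This stands. It finds near hits and misses in the full feature space, so it can pick up interactions. Only the narrower statement holds: it does not penalise redundancy.
- **Detection performance is measured.** This stands. The selected features go through LOSO validation with accuracy per subject. A reader might infer that the recommendation would rest on no performance data at all, and the article does not support that. What is missing is the performance of rival sensor sets.
- **The harm may be small.** This stands. The simulation uses exact duplicates and assumed separations. Nothing in the article shows that left and right sensors are near-duplicates, and recording the laterality of symptoms suggests that asymmetry may matter. A tree limited to 5 or 10 splits also cannot use every duplicate it is offered.
- **A fuller plan may list the sensor sets.** This stands only in part. The Discussion and Conclusions do express an intention to evaluate placements. But the Primary Outcome section fixes the rule that turns the ranking into sensors, and Features Extractions fixes the method. A fuller plan would have to replace or add to that rule, not merely fill in detail. The reason for preferring Relief-F is referred to a cited source that was not available here.

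**Conclusion.** The point holds as a mismatch between objective and analysis. The objective is stated in two ways, and the analysis described does not establish the one in the Introduction. The procedure gives no evidence that the selected sensors are the optimal combination.

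A reader might go further and infer that the analysis cannot reach the optimal set, or that the sensors it names will be wrong. The article does not support either: the ranking could coincide with the best set, but the plan as described would not show it.

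The size is certain on one count: no sensor set, of 15 or 127, is compared with another by design. The cost in accuracy is uncertain. Under the assumed inputs it ran from nil to about 9 percentage points, and was near 1 point or less with 20 features. This should be changed before the analysis. It does not invalidate the data being collected.

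**What to change.** State one primary objective, in the same words in the Introduction and the Primary Outcome section. Then take one of two routes.

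**If the objective is the optimal combination:**
1. Pre-list the candidate sets: the 15 location sets, or the 127 sets of individual sensors if one-sided placement is of interest.
2. Fit each set using only its own features. Make feature selection, tuning and the choice of set inside the LOSO training folds. This needs an inner loop, which the plan does not now have.
3. Compare held-out performance per patient, paired by patient, with a patient-level interval (for example a bootstrap over patients).
4. Pre-state the selection rule, such as the smallest set within a stated tolerance of the best, and give the tolerance.
5. Use Relief-F only within a set, or with a redundancy filter applied inside each training fold.

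**Otherwise:** limit the objective and conclusions to a ranking of features and locations, and do not claim an optimal combination.

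**Cost:** analysis text and computing time. All seven sensors are already worn and recorded, and the analysis starts only after data collection. With at most 32 settings, the candidates number 15 × 32 = 480 or 127 × 32 = 4,064; with 8 settings, 15 × 8 = 120 or 127 × 8 = 1,016. Under an inner LOSO with 18 patients, 480 candidates mean 480 × 17 × 18 = 146,880 fits of trees with at most 10 splits. The main downside is statistical: 18 patients may not separate similar sets. That is a reason to fix the tolerance rule in advance and to report the intervals.
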